#### Inclusion criteria

1.4.1

1.First-ever stroke and in stable condition after acute management of ischemic stroke.2.Aged between 35 and 85, male or female.3.Responsible focuses of the unilateral white matter area indicated by cranial CT or MRI.4.No more than 14 days from stroke onset, with unilateral limb movement dysfunction and be proved to be right handed after standardized testing.5.National Institute of Health Stroke Scale (NIHSS) scores from 2 to 20, Grading Muscle Strength of paralyzed upper limbs between grade 1 and grade 4, and have not received any standard rehabilitation intervention before inclusion.6.Sign the informed consent by the patient himself or voluntarily.

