#### Primary outcome

1.6.1

Primary outcomes will be conducted before and after rehabilitation therapies, including sum of bilateral activated volume of primary motor (M1), supplementary motor area (SMA), premotor cortex (PMC) (V_M1+SMA+PMC_); lateralization index (LI) of interhemispheric M1, SMA, and PMC (LI_M1+SMA+PMC_)(LI = (ΣV_C_ − ΣV_I_)/(ΣV_C_+ ΣV_I_), subscripts C and I refer to contralateral and ipsilateral hemisphere responses, respectively. The ΣV measures the regional activation level associated with the activated voxel); functional connectivity of bilateral M1, SMA, PMC, and the value of fractional anisotropy (FA) in corticospinal tract (CST) at ipsilesional posterior limb of internal capsule. Data will be collected before (at basement) and after (3 months) rehabilitation.

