### Data acquisition and preprocessing

1.7

Data will be acquired by a Siemens 3.0T Magnetom Trio scanner (Siemens Medical Solutions). Subjects will receive 2 MRI sessions (1 before and 1 after rehabilitation therapy). Each session included 1 rs-fMRI scan, 1 task functional scan and 1 DTI scan. For fMRI scan, parameters are TR/TE/FA = 1500 ms/30 ms/90°, 200 time points, resolution = 3.4 × 3.4 × 5 mm^3^, 21 axial slices. During rs-fMRI scan, patients will be asked to keep away with the eyes closed and think of nothing. The motor task scans used a block design paradigm consisting of alternating 30-seconds periods of performance of an isometric precision grip task and rest for 4 minutes. DTI images will be acquired with the following parameters: matrix size = 94 mm × 94 mm, field of view = 240 mm × 240 mm, 2.6 mm slice thickness, 56 slices. We acquired 1 set of 30 diffusion weighted images with a *b*-value = 1000 s/mm^2^, and 5 no diffusion weighted images.

All data will be analyzed using Functional MRI of the Brain (FMRIB's) Software Library (FSL) tools. Functional data sets will undergo slice timing correction, motion correction, scaling to percent signal change, smoothed with a Gaussian kernel of 8 mm full-width-at-half maximum, bandpass temporal filtering (0.01–0.08 Hz), and grand mean intensity normalized. A whole brain analysis of white matter integrity between groups will be performed to investigating FA. FA quantifies the degree to which water diffusion will be restricted and calculated based on the diffusion tensor. The data will be corrected for head motion and eddy current distortion, and brain extracted using Brian Extraction Tool. FA images will be then created by fitting the data to a tensor model at each voxel using DTI fit within the FMRIB's Diffusion Toolbox. Lesion will be masked out in each subject's data so that all analyses are performed on nonlesioned data.

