### Definition of ROI and lesion

1.8

We choose three pairs of seeds in sensorimotor network, the bilateral primary motor (M1), supplementary motor area (SMA), and premotor cortex (PMC). Hand movement is most closely related to M1.^[20,21]^ The early involvement of the SMA in the process of stroke recovery and correlation of initial activation of the SMA with motor recovery were demonstrated.^[22,23]^ PMC might influence other cortical areas in the surviving motor network to support residual motor output and higher order processes required for motor function.^[24]^ A 6-mm radius sphere will be placed at the above 3 pairs of seeds to generate the regions of interest (ROI).

Lesions will be drawn in each patients’ structural space on the T1-weighted images using the co-registered T2-weighted diffusion images as a reference for lesion extension. The lesion mask is nonlinearly registered into standard space using FMRIB's Non-linear Registration Tool (FNIRT) with an affine transformation (12 degrees of freedom). The lesion mask will be also used during the registration steps of the structural, resting state fMRI, and DTI data so that voxels in the lesioned area would be excluded from the normalization procedure.

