### Data analyses

1.9

Data analysis will be handled by independent statisticians who are blind to the groups. The statistical tests will be 2-side and at the 5% significance level. Means and standard deviation will be used for statistical description of continuous variables. For fMRI data, independent sample *t*-test or independent sample rank test will be used for grouped comparison of quantitative data. Pearson correlation coefficients (*r*) will be used to determine whether patients’ functional connectivity correlated with their FMA score and be computed after application of Fisher's *r*-to-*z* transform to yield variates that are approximately normally distributed (*z* = 0.5 ln[(1+*r*)/(1−*r*)]). All the statistical analysis will be carried out by the SPSS software (Armonk, NY). For DTI data, statistical analyses will be performed using nonparametric permutation testing (Randomize in FSL) with 5000 Monte Carlo simulations. We looked for differences in FA between the groups accounting for age, time of stroke onset, and NIHSS as regressors of no interest in the general linear model.

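### The primary FA outcome is a value at one tract location on the lesion side, but the only FA analysis stated is a whole-brain group comparison, which neither estimates nor tests that value

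*Protocol article*

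**What the plan says.** **Outcome.** Section 1.6.1 lists several primary imaging measures. The diffusion measure is "the value of fractional anisotropy (FA) in corticospinal tract (CST) at ipsilesional posterior limb of internal capsule". On timing, the same section says "Data will be collected before (at basement) and after (3 months) rehabilitation". The endpoint is therefore one regional value per patient per session, tied to the side of the lesion.

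**Scope of the FA analysis.** Section 1.7 says "A whole brain analysis of white matter integrity between groups will be performed to investigating FA". It also says that "FA images will be then created by fitting the data to a tensor model at each voxel" and that "Lesion will be masked out in each subject's data so that all analyses are performed on nonlesioned data".

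**Test.** For diffusion data, section 1.9 says that "statistical analyses will be performed using nonparametric permutation testing (Randomize in FSL) with 5000 Monte Carlo simulations". The accompanying model compares FA between the groups with age, onset time and NIHSS as nuisance covariates. The t-test or rank test in the same section is introduced for fMRI data only.

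**Regions and side.** Section 1.8 defines seed spheres for M1, SMA and PMC; no tract or capsule region is described. Section 1.4.1 requires "Responsible focuses of the unilateral white matter area indicated by cranial CT or MRI", without restricting the side.

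**The concern.** The outcome section asks whether FA at one named place on the lesion side differs between arms. The analysis sections ask whether FA differs between arms somewhere in the brain. These are different questions, and the output of the second does not contain the answer to the first. A whole-brain map normally includes the voxels of the internal capsule, but searching them gives no patient-level estimate of the named value, no confidence interval and no single test.

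The consequence is that one of the primary outcomes has no analysis attached to it. The choice of region, of how to handle lesion side, and of threshold would remain open after the maps had been seen.

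**Working it through.** **1. The passages side by side**

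| Feature | Outcome (1.6.1) | FA analysis (1.7 and 1.9) |
|---|---|---|
| Location | CST at the posterior limb of the internal capsule | Whole brain, no region named |
| Side | Ipsilesional | Not mentioned |
| Time | Baseline and 3 months | Not stated whether 3-month FA or change is compared; baseline FA is not among the covariates |
| Result | One value per patient per session | A between-group comparison across an FA map |

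The one route that would suit a single value per patient, the t-test or rank test, is stated for fMRI data. No sentence connects the regional FA value to any test.

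**2. What is inferred.** The article does not call the group test voxelwise. That reading follows from the whole-brain scope, from FA maps fitted voxel by voxel, and from the FSL permutation tool. The tool can also be run on a region or a single value, but no such use is stated.

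**3. Size, as illustration only.** The plan gives no power figure to reproduce. Inputs from the document: 40 patients at 1:1, so n = 20 per arm, and a two-sided 5% level. Assumptions: a true difference d = 1.0 SD, no dropout, covariates ignored, and m effective independent tests with threshold 0.05/m.

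Noncentrality: d × √(n/2) = 1.0 × √10 = 3.162, with 2n − 2 = 38 degrees of freedom. Power is the probability that a noncentral t with these parameters exceeds the two-sided critical value in absolute size.

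| m | Level 0.05/m | Critical t | Power at one location |
|---|---|---|---|
| 1 (one regional test) | 0.05 | 2.024 | 87% |
| 10 | 0.005 | 2.980 | 58% |
| 100 | 0.0005 | 3.806 | 29% |
| 1000 | 0.00005 | 4.572 | 11% |

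If no correction is applied across the map, these losses do not arise. Each location is then tested at 5%, and the chance of a false positive somewhere in the brain is not controlled.

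**4. Number of permutations.** The Monte Carlo standard error at p = 0.05 is √(0.05 × 0.95/5000) = 0.003. The 5000 simulations are not the problem.

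**5. Lesion side.** Suppose a fraction q of patients has a left-sided lesion, the effect δ exists only on the lesion side, and images are not aligned. The expected difference is then qδ at a left-capsule voxel and (1 − q)δ at the matching right-capsule voxel. The document does not give q, so the dilution cannot be quantified.

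**The case against.** **Regional extraction may simply be left to the full protocol or SAP.** This is the strongest objection. How a capsule region is drawn is a detail an article often omits, and section 1.8 concerns the sensorimotor network seeds, so its silence does not prove that no capsule region exists. That stands as far as the drawing of the region goes. It does not remove the mismatch: the article does not stop at naming the outcome but assigns FA an analysis, with scope, method and covariates, and that analysis has a different target.

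**A reader might infer that the plan incurs a large power loss.** The documents do not support this as a flat statement. No correction across voxels is stated, so the loss depends on one being applied. The test counts and the 1.0 SD difference are assumptions, and the plan claims no power that could be contradicted.

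**A reader might infer that the comparison mixes ipsilesional and contralesional tissue and halves the effect.** The article is silent on alignment; it does not say that images are left unaligned. Halving to 0.5 SD (34% power for one test at 5%) would also need an even left/right split, no contralesional effect and an unchanged SD. The documents give none of these.

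**This is a 40-patient exploratory pilot, and FA is one of several primary measures.** True, and it limits the consequences. The other primary measures are fMRI-based and do have a stated test. A pilot that names a primary outcome still needs an analysis that reports it.

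**Conclusion.** The point holds as a mismatch between a primary outcome and its stated analysis. Followed as written, the plan neither estimates nor tests FA in the CST at the ipsilesional posterior limb. This rests on the text alone and on no numerical assumption.

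The power figures show only that the two analyses are not interchangeable: 87% for one regional test, against 58% to 11% at one location under an assumed correction for 10 to 1000 tests. Dilution from unaligned lesion sides is possible but of unknown size.

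**What to change.** 1. In section 1.9, state that mean FA of the CST at the ipsilesional posterior limb is extracted for each patient and session. Define the region, and say what is done when the lesion mask overlaps it, since lesioned voxels are removed from all analyses.
2. Compare arms on the 3-month value in one linear model with baseline FA, age, onset time and NIHSS. Report the adjusted difference with its confidence interval. A permutation p-value is acceptable.
3. Keep the whole-brain map, label it exploratory, and state that images are aligned to one lesion side and that a family-wise corrected threshold is used.

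Naming the regional test and relabelling the map resolve the mismatch itself. Baseline adjustment and side alignment are improvements that use data already planned.

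Cost: a few sentences of analysis text and one region extraction per scan. There are no additional patients, visits or scans.

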### Definition of ROI and lesion

1.8

We choose three pairs of seeds in sensorimotor network, the bilateral primary motor (M1), supplementary motor area (SMA), and premotor cortex (PMC). Hand movement is most closely related to M1.^[20,21]^ The early involvement of the SMA in the process of stroke recovery and correlation of initial activation of the SMA with motor recovery were demonstrated.^[22,23]^ PMC might influence other cortical areas in the surviving motor network to support residual motor output and higher order processes required for motor function.^[24]^ A 6-mm radius sphere will be placed at the above 3 pairs of seeds to generate the regions of interest (ROI).

Lesions will be drawn in each patients’ structural space on the T1-weighted images using the co-registered T2-weighted diffusion images as a reference for lesion extension. The lesion mask is nonlinearly registered into standard space using FMRIB's Non-linear Registration Tool (FNIRT) with an affine transformation (12 degrees of freedom). The lesion mask will be also used during the registration steps of the structural, resting state fMRI, and DTI data so that voxels in the lesioned area would be excluded from the normalization procedure.

### Data analyses

1.9

Data analysis will be handled by independent statisticians who are blind to the groups. The statistical tests will be 2-side and at the 5% significance level. Means and standard deviation will be used for statistical description of continuous variables. For fMRI data, independent sample *t*-test or independent sample rank test will be used for grouped comparison of quantitative data. Pearson correlation coefficients (*r*) will be used to determine whether patients’ functional connectivity correlated with their FMA score and be computed after application of Fisher's *r*-to-*z* transform to yield variates that are approximately normally distributed (*z* = 0.5 ln[(1+*r*)/(1−*r*)]). All the statistical analysis will be carried out by the SPSS software (Armonk, NY). For DTI data, statistical analyses will be performed using nonparametric permutation testing (Randomize in FSL) with 5000 Monte Carlo simulations. We looked for differences in FA between the groups accounting for age, time of stroke onset, and NIHSS as regressors of no interest in the general linear model.

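### Four co-equal primary outcomes, one of them a set of connectivity values with no summary, are tested at a flat 5% with no lead outcome, order or adjustment

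*Protocol article*

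**What the plan says.** Section 1.6.1 (Primary outcome) of the protocol article speaks in the plural: "Primary outcomes will be conducted before and after rehabilitation therapies". It then lists four kinds of measure.

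- Activated volume: "sum of bilateral activated volume of primary motor (M1), supplementary motor area (SMA), premotor cortex (PMC"), with one summed index.
- Laterality: "lateralization index (LI) of interhemispheric M1, SMA, and PMC", also with one combined index.
- Connectivity and FA: "functional connectivity of bilateral M1, SMA, PMC, and the value of fractional anisotropy (FA) in corticospinal tract (CST"). FA is located at one site, the posterior limb of the internal capsule on the lesion side. Connectivity has no combined index.

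Section 1.8 (Definition of ROI and lesion) gives the seeds: "We choose three pairs of seeds in sensorimotor network", left and right for each of M1, SMA and PMC, so six regions.

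Section 1.9 (Data analyses) sets one significance level: "The statistical tests will be 2-side and at the 5% significance level". For fMRI measures a t-test or "independent sample rank test will be used for grouped comparison of quantitative data". For DTI it specifies permutation testing with 5000 simulations. It does not say whether that includes a voxel-wise correction.

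On framing, the Abstract and Section 1.3.1 call the study a pilot of 40 patients, and Section 1.1.1 words the main aim as exploring mechanisms. The Aims paragraph of the Abstract, however, also sets out to establish efficacy, and the Background seeks stronger evidence for home-based rehabilitation.

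**The concern.** The four primary outcomes serve the trial's main aim, the mechanism of recovery. The article does not say which of them carries that aim, whether one significant result is enough, or whether all are needed. Under a per-test 5% level, any one of them, or any one connection within the third, could be presented as a significant primary finding. The error rate of such a claim is then not 5%.

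The choice of primary outcome belongs in a protocol and is not a detail left to an analysis plan. The article makes that choice, and makes it in a form that leaves the error rate of the main claim open. A later analysis plan that wished to add a correction would first have to decide what the primary connectivity measure is.

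**Working it through.** There is no figure in the plan to reproduce. The 5% is a setting, and no family-wise error rate is stated.

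**Inputs from the article**
- Level: two-sided 0.05 (Section 1.9).
- Single-value primary outcomes: 3, namely volume, laterality and FA (Section 1.6.1).
- Seeds: 6 (Section 1.8). Homologous left-right connections: 3. All pairwise connections: 6 × 5 / 2 = 15.
- Sample: 40, allocated 1:1, so 20 per arm (Section 1.3.1).

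**Assumptions**
- One between-group comparison per measure.
- No true effect on any measure.
- Correlations among measures as shown below; the article gives none.

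**Number of tests, k**
- Connectivity as one value: 3 + 1 = 4.
- Three homologous pairs: 3 + 3 = 6.
- All connections: 3 + 15 = 18.

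**Independent tests.** The chance of at least one false positive is 1 − 0.95^k:
- k = 4: 18.5%
- k = 6: 26.5%
- k = 18: 60.3%

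It passes one half between k = 13 (48.7%) and k = 14 (51.2%). Since 14 = 3 + 11, that needs at least 11 of the 15 connections to be tested, even with full independence.

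**Correlated tests.** Simulated two-sample t-tests, 20 per arm, 40,000 replicates:

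| Correlation among connections | Correlation elsewhere | k = 4 | k = 6 | k = 18 |
|---|---|---|---|---|
| 0 | 0 | 18.8% | 26.6% | 60.5% |
| 0.3 | 0 | 18.7% | 26.0% | 53.6% |
| 0.5 | 0 | 18.8% | 25.2% | 45.7% |
| 0.5 | 0.3 | 17.7% | 23.6% | 43.7% |
| 0.7 | 0.3 | 17.4% | 22.3% | 34.6% |
| 0.8 | 0.5 | 15.5% | 19.2% | 27.5% |

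The first row agrees with the formula within simulation error. The overall range, 15.5% to about 60%, is roughly 3 to 12 times the nominal 5% (15.5 / 5 = 3.1; 60.3 / 5 = 12.1).

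**Not counted.** The choice between t and rank test, the correlations of connectivity with FMA (Section 1.9) and the whole-brain FA comparison (Section 1.7) would add further looks at the data.

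**What a correction across all tests would cost.** Bonferroni uses 0.05 / k: 0.0125, 0.00833 and 0.00278 for k = 4, 6 and 18. This holds the family-wise rate at 5% or below. Power by normal approximation is Φ(d × √(n/2) − z), where z is the two-sided critical value. With n = 20 and an assumed standardised difference d = 0.8, d × √(n/2) = 0.8 × √10 = 2.53:
- level 0.05: Φ(2.53 − 1.96) = 72%
- k = 4: 51%
- k = 6: 46%
- k = 18: 32%

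Naming one primary outcome keeps 5%, and the 72%, for that outcome.

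**The case against.** The strongest reply is that this is a small pilot with an exploratory aim. It makes no confirmatory claim, and a pilot need not define success. Section 1.9 gives only a general level and does not say that no correction will be used; a correction could stand in an analysis plan that is not shown. There are also partial safeguards. The kinds of outcome are named in advance, assessors and analysts stay blind until analysis is finished (Section 1.3.2), and Section 1.12 promises publication whatever the direction of effect.

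Part of this stands. The absence of a named correction would be weak ground by itself, and the pilot framing makes the problem less serious. It does not remove it, because the article labels the outcomes primary, attaches a significance level and states an efficacy aim. That aim may rest mainly on FMA, the secondary outcome, so the primary label and the 5% level weigh most here. Blinding and a promise to publish do not control the error rate across outcomes or fix which connection counts. Any voxel-wise correction for FA would act within FA, not across the four outcomes.

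Three stronger readings are tempting, and the article does not support them.

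- A reader might infer that a false-positive mechanism is likely. The chance exceeds one half only if most of the 15 connections are tested and they are weakly correlated; with four to six tests it is about 16% to 27%.
- A reader might infer that the plan commits to 15 connections. It does not. Three homologous pairs is a natural reading of the text, and 15 is only the upper bound that the text leaves open.
- A reader might infer that the outcome to highlight will be picked after the results are seen. The plan leaves room for that, but it is a risk, not a stated intention.

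**Conclusion.** The point holds in a limited form. The article fixes four co-equal kinds of primary outcome, leaves one as an undefined set, and applies 5% to each test with no lead outcome, order or adjustment. With no true effect, the chance of at least one false-positive primary result is about 16% to 27% if connectivity is one value or three pairs, and about 28% to 60% if all 15 connections are tested. These ranges rest on the assumed test counts and correlations, and on one between-group comparison per measure.

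Given the pilot framing, this should be fixed but is not a fatal fault. It is best settled before results are seen.

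**What to change.** Either of two changes to the wording of Sections 1.6.1 and 1.9 would do.

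1. Name one primary outcome, tested at two-sided 5%: volume, laterality, one pre-named connection, or FA at the stated site. Make the others secondary under Holm. Reduce connectivity to one pre-named summary, or control the false discovery rate within the connectivity set. Say whether FMA, already a secondary outcome in Section 1.6.2, belongs to the Holm family.
2. In keeping with the pilot framing, label all four outcomes exploratory, report estimates with 95% confidence intervals, and drop the 5% significance claim for them.

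Neither changes recruitment, assessments or treatment. The downside is fewer nominally significant results and, under the first option, less power for the outcomes that are not chosen.

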#### Randomization

1.3.1

In this pilot study, we aim to collect 40 patients diagnosed as stroke from the Department of Neurology, Shanghai the Fifth People's Hospital, Fudan University. Patients included in the study will be randomly allocated into 2 groups in a ratio of 1:1 after baseline assessment: home-based rehabilitation group and conventional rehabilitation group. An independent statistician will conduct randomized allocation by using a computer. The former will receive exercise training rehabilitation and electromyography-triggered neuromuscular stimulation with the assistance of caregivers at home. Specialist physicians will evaluate the recovery condition of patients via telerehabilitation system every week and give guidance on rehabilitation training and electro-stimulation therapy. The latter will receive the same rehabilitation training under the guide of specialist physicians face to face. Specialist physicians will evaluate the recovery condition of patients at outpatient clinic every week and adjust the rehabilitation strategies. Allocation concealment will be guaranteed, since allocation information will be protected in opaque sealed envelopes by a specially assigned person who is not involved in the study.

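### The imaging comparisons between arms name no baseline covariate and do not state the compared value; adjusting each 3-month outcome for its own baseline would add precision without new data

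*Protocol article*

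**What the plan says.** All of the following is in the Protocol article.

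- **Design.** Under Randomization (1.3.1), "we aim to collect 40 patients diagnosed as stroke", and they are "randomly allocated into 2 groups in a ratio of 1:1 after baseline assessment". The baseline scan can therefore serve as a covariate measured before allocation.
- **Timing.** The Primary outcome section (1.6.1) covers activated volume, lateralization index (LI), functional connectivity and corticospinal-tract FA, and states: "Data will be collected before (at basement) and after (3 months) rehabilitation". Data acquisition and preprocessing (1.7) agrees: "Subjects will receive 2 MRI sessions (1 before and 1 after rehabilitation therapy").
- **fMRI comparison.** Data analyses (1.9) names a two-sample t-test, or an "independent sample rank test will be used for grouped comparison of quantitative data". It names no covariate and does not define the quantity compared.
- **FA comparison.** The same section looks for group differences in FA by permutation testing, "accounting for age, time of stroke onset, and NIHSS as regressors of no interest in the general linear model". Baseline FA is not in that list, and no change-in-FA image is described.
- **Error level.** "The statistical tests will be 2-side and at the 5% significance level".

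**The concern.** For a continuous outcome measured before and after treatment, the patient's own baseline value is often the best single predictor of follow-up. Section 1.9 chooses tests that take no covariate for the fMRI outcomes. It chooses a covariate list for FA that omits baseline FA. Because the article itself fixes these tests and this list, the point is not just detail left to a fuller document.

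Two things are at stake. The first is precision, which is scarce with about 20 patients per arm. The second is how a chance baseline difference is handled. Entry is wide ("National Institute of Health Stroke Scale (NIHSS) scores from 2 to 20"), so patients may differ considerably at the first scan. Such a gap passes partly into a comparison of follow-up values. A comparison of changes subtracts it in full, which is too much whenever the correlation between the two scans is below 1.

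**Working it through.** **Inputs from the article:** 40 patients, 1:1, so n = 20 per arm; two-sided alpha 0.05. The article gives no effect size, SD or power behind the 40, so there is no stated figure to reproduce.

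**Assumptions:** equal SD at baseline and 3 months, set to 1; approximate normality; baseline to 3-month correlation rho, which the article does not give, shown from 0.1 to 0.7.

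**Variance of the outcome per patient under each analysis:**
- follow-up value only: 1
- change score: 2(1 − rho)
- baseline-adjusted (ANCOVA): 1 − rho²

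Estimating the baseline slope costs an average variance factor of about 1 + 1/36 at 40 patients. Results are given without and with it.

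**Detectable difference.** The standard error of the arm difference is sqrt(2v/20), with v from the list above. Power comes from the noncentral t distribution, with 38 degrees of freedom for the t-test and 37 for ANCOVA. The t-test on follow-up values detects 0.909 SD at 80% power, and has 45.6% power for an assumed true difference of 0.6 SD.

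| rho | ANCOVA variance / follow-up-only variance, 1 − rho² | Detectable SD, without / with slope cost | Power at 0.6 SD, without / with slope cost |
|---|---|---|---|
| 0.1 | 0.99 | 0.905 / 0.918 | 45.9% / 44.9% |
| 0.3 | 0.91 | 0.868 / 0.880 | 49.1% / 48.0% |
| 0.5 | 0.75 | 0.788 / 0.799 | 56.9% / 55.8% |
| 0.7 | 0.51 | 0.650 / 0.659 | 73.5% / 72.3% |

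**Against change scores.** The variance ratio is (1 − rho²) / [2(1 − rho)] = (1 + rho)/2, which is 0.65, 0.75 and 0.85 at rho 0.3, 0.5 and 0.7. ANCOVA is thus also more precise if section 1.9 intends changes, most clearly at low rho.

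**Chance imbalance.** The standard error of a baseline difference is sqrt(2/20) = 0.316 SD. A gap above 0.5 SD in either direction has probability 2[1 − Φ(0.5/0.316)] = 11.4% for any one measure. A gap of 0.5 SD shifts the estimates as follows:
- follow-up values, by rho × 0.5: 0.15, 0.25 and 0.35 SD at rho 0.3, 0.5 and 0.7
- changes, by (rho − 1) × 0.5: −0.35, −0.25 and −0.15 SD
- ANCOVA: no shift on average

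**Error rates.** In simulation with no true effect (15,000 trials per rho), type I error over all trials was about 5% for all three analyses. Among trials with a baseline gap above 0.5 SD, at rho 0.3 / 0.5 / 0.7, it was:
- follow-up values: 8.7% / 13.6% / 22.7%
- change scores: 16.9% / 13.8% / 10.2%
- ANCOVA: 5.2% / 5.0% / 4.3%

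**The case against.** **A reader might infer that the plan ignores the baseline scan.** The text does not establish this. Section 1.9 does not say which value is compared, and the Background speaks of dynamic changes. A t-test on change scores fits the wording and would use the baseline. Nor does the FA sentence name a time point, so a change image is not excluded. What stands is that the compared quantity is unstated and no same-measure baseline covariate is named.

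**A reader might infer that the tests are invalid.** They are not. Under 1:1 randomisation, unadjusted tests keep their 5% level over all possible allocations. The raised error rates above apply only to the minority of trials with a large chance gap. The trial is also a pilot that admits its small sample and makes no power claim that could fail.

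**The gain depends on a correlation that the article does not give.** Patients enter within 14 days of stroke and are rescanned after 3 months, so a low rho cannot be ruled out. At rho 0.3 the gain over follow-up values is small. At 0.1, once slope estimation is counted, adjustment is marginally worse (0.918 against 0.909 SD). This objection stands and limits the size of the point, but the possible loss is trivial beside the possible gain.

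**Two further inferences should not be drawn.** Nothing in the article shows that NIHSS affects all outcomes alike, so its use for DTI alone is not in itself an error. And the lack of a stated between-arm test for the Fugl–Meyer score is something a condensed article may leave to the full protocol or analysis plan.

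**Conclusion.** The point holds as an improvement. Section 1.9 fixes between-arm analyses that name no same-measure baseline covariate, and it leaves open whether the 3-month value or the change is tested, although every imaging outcome is measured at baseline. The consequence is lost precision and poor handling of chance imbalance, not a wrong overall error rate.

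Measured against a t-test on follow-up values, the saving in detectable difference runs from essentially nothing at rho 0.1 to about 0.26 SD at rho 0.7 (0.909 − 0.650 without slope cost; 0.25 with it). Measured against change scores, ANCOVA has 65% to 85% of the variance over rho 0.3 to 0.7. These figures rest on 20 analysed patients per arm, equal SDs at both scans, approximate normality and an assumed rho. They describe a single outcome value per patient. For the FA model, age, time from onset and NIHSS may already carry part of the baseline information, so the added gain there may be smaller; the article gives no figure from which to work it out.

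**What to change.** In section 1.9:

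- State that the analysed quantity is the 3-month value.
- For activated volume, LI, each connectivity z-value and corticospinal-tract FA, fit a linear model on arm plus the baseline value of the same measure. Report the adjusted difference with its 95% confidence interval.
- Where residuals are skewed, take a permutation p-value from that same model, in place of a choice between t and rank tests.
- In the whole-brain FA permutation model, add baseline FA as a voxelwise covariate.

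If the investigators prefer to present change, a model of change on arm and baseline gives the same arm difference as the model of the 3-month value.

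The cost is a revision of the analysis text, one degree of freedom per model, and a trivial loss of precision if the baseline to 3-month correlation is near zero. No extra scan, visit or patient is needed, and permutation testing is already planned for the DTI data.
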